## 6. Ethical Considerations

The investigator will ensure that this study is conducted in full conformity with the principles set in the Declaration of Helsinki. The protocol will be submitted for Ethical Commission approval.

Exercise intervention in the elderly population (III), was already submitted and accepted by the ethical commission (**Attachment 6**).

For the illness-prone evaluation profile (II), baseline assessment procedure as well as measurements were previously submitted and accepted by the ethical commission in association with the project - Mechanisms of airway damage in elite swimmers (**Attachment 5**).

The investigator will invite the participant to enroll the study participation after explaining the aims and goals of the study. A written information about each study will be provided to the participant (**Attachments V and VI** - presented in the ethical submission dossier). Consent forms and patient information will be given and the subject will be asked to read and review the documents carefully, the participant don't need to decide at that moment and time will be provide for reflecting about the decision to enroll the study. Upon reviewing the consent form and information, the investigator will explain the research study to the subject and answer any questions that may arise. The subject will then sign the informed consent document prior to any procedures being done specifically for the study. The subjects may withdraw consent at any time throughout the course of the trial. A copy of the informed consent document will be given to the subjects for their records. The rights and welfare of the subjects will be protected by emphasizing to them that the quality of their medical care will not be adversely affected if they decline to participate in this study. No minors will participate in these studies.

Subject confidentiality is strictly held in trust by the participating investigators. This confidentiality is extended to the clinical information relating to participating subjects.

The study protocol, documentation, data, and all other information generated will be held in strict confidence. No information concerning the study or the data will be released to any unauthorized third party. In the event of studies' discontinuation, patients will not be affected.

Confidentiality of the data will be preserved by the investigation groups and the acquired information will only be used for the purposes of this project. Study will end when the time limit for sending the questionnaires is achieved. The final aim of this study will be scientific publication.

### Data Handling and Record Keeping

The investigator is responsible to ensure the accuracy, completeness, legibility, and timeliness of the data reported. All source documents should be completed in a neat, legible manner to ensure accurate interpretation of data. When making changes or corrections, cross out the original entry with a single line, and initial and date the change.

Copies of the electronic clinical form will be provided for use as source documents and maintained for recording data for each subject enrolled. Data reported in the electronic clinical form derived from source documents should be consistent with the source documents or the discrepancies should be explained. All source documents and laboratory reports must be reviewed by the clinical team and data entry staff, who will ensure that they are accurate and complete.

Data collection is the responsibility of the clinical trial staff. During the study, the investigator must maintain complete and accurate documentation for the study.

Clinical data (including demographic data, questionnaires, outcome measures, adverse events, concomitant medications, and expected adverse reactions data) as well as laboratory data will be entered into a database in a data system. This data system includes password protection and internal quality checks, such as automatic range checks, to identify data that appear inconsistent, incomplete, or inaccurate.

## 7. MILESTONES

|                 |                                                                                                                                                             |                                                                                                                                                                                                                                                                            |
|-----------------|-------------------------------------------------------------------------------------------------------------------------------------------------------------|----------------------------------------------------------------------------------------------------------------------------------------------------------------------------------------------------------------------------------------------------------------------------|
| I        | Cross-cultural translation and validation of Wisconsin Upper Respiratory Symptom Survey (WURSS-21) for upper respiratory tract infections monitoring | Cross-cultural translation and validation of a measuring tool to be applied in upper respiratory tract infection assessment. Validation of a measure that can be further used in respiratory tract infection assessment.                                                   |
| Month 28        | Cross-cultural translation concluded                                                                                                                        |                                                                                                                                                                                                                                                                            |
| Month 34        | Questionnaire validation                                                                                                                                    |                                                                                                                                                                                                                                                                            |
| II       | Upper respiratory tract infection susceptibility in athletes – a 3 months follow-up study                                                            | Total number of participants assembled for follow-up procedure.
Laboratory analysis will be performed in association with statistic analysis as only the urine that was obtained during an infection period will be analyzed                                            |
| Month 28        | Recruitment and baseline evaluation concluded                                                                                                               |                                                                                                                                                                                                                                                                            |
| Month 31        | Follow-up termination and urine collection                                                                                                                  |                                                                                                                                                                                                                                                                            |
| Month 37        | Laboratory analysis and statistical analysis concluded                                                                                                      |                                                                                                                                                                                                                                                                            |
| III      | Effect of physical training on respiratory tract infections in the elderly                                                                           | Total number of participants assembled for intervention procedure
Laboratory analysis will be done a posteriori and statistical analysis will occur at the same time in order to evaluate which patients had respiratory infections                                     |
| Month 4         | Recruitment and allocation concluded                                                                                                                        |                                                                                                                                                                                                                                                                            |
| Month 10        | Exercise program intervention and respiratory symptoms questionnaire assembly                                                                               |                                                                                                                                                                                                                                                                            |
| Month 18        | Laboratory and statistical analysis concluded                                                                                                               |                                                                                                                                                                                                                                                                            |
| Month 30 | Study I, II, III publication                                                                                                                         |                                                                                                                                                                                                                                                                            |
| IV       | Effect of an high fat versus healthy diet meal on neuroimmunendocrine response to exercise                                                           | Randomization procedures will be performed alongside the recruitment and baseline achievement. After recruitment intervention can be performed. Both interventions will be done in parallel but independent from one another despite coming from same recruited population |
| V        | Effect of physical activity on immunity                                                                                                              |                                                                                                                                                                                                                                                                            |
| Month 39        | Recruitment concluded                                                                                                                                       |                                                                                                                                                                                                                                                                            |
| Month 39        | Randomization to meal and physical activity                                                                                                                 |                                                                                                                                                                                                                                                                            |
| Month 42        | Meal challenge followed by exercise intervention concluded                                                                                                  |                                                                                                                                                                                                                                                                            |
| Month 44        | Reducing physical activity intervention concluded                                                                                                           |                                                                                                                                                                                                                                                                            |
| Month 45        | Assessment of safety and adverse events concluded, in order to evaluate long term changes                                                                   |                                                                                                                                                                                                                                                                            |
| Month 50        | Laboratory analysis concluded
Statistical analysis concluded                                                                                             |                                                                                                                                                                                                                                                                            |
| Month 52 | Theses presentation, Study IV and V publication                                                                                                      |                                                                                                                                                                                                                                                                            |

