### **4.1.3. Effect of Physical training on respiratory tract infection in the elderly (III)**

*This study was previously presented and accepted by the ethical commission of Centro Hospitalar de São João (Attachment 6)*

The study was a non-randomized, un-blinded, controlled trial targeting patients over 60 years recruited by the Exercise Health for the Elderly program, coordinated in Sports Faculty of Porto University, from senior universities and nursing homes from Northern Portugal area. The selected participants performed a 36 week, 3 times per week, exercise-training program in the Sports University of Porto, with aerobic and anaerobic components using an individualized protocol by trained sports personal. During this period of time, respiratory tract infections were monitored through a symptoms diary and respiratory infections were defined as severe, moderate or mild accordingly to the symptoms assembly. Previously to the intervention a global physical condition was assessed (weight, height, heart rate, functional fitness and blood pressure were measured), co-morbidities were registered (hypertension, dyslipidemia, diabetes, ischemic heart disease, previous stroke, previous cancer diseases, osteo-articular and osteoporosis), as well as smoking habits, influenza immunization status and if they previously practiced exercise.

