### Respiratory Infections Symptoms Diary

For respiratory infections measure it was used a symptom diary, based in previously published symptoms diaries and common cold assessment questionnaires based in the Jackson index, Common Cold Questionnaire and Wisconsin diary symptoms short form-survey[45, 46]. The diary was built to answer to the specific demands of the population, namely age, real life conditions of the study as no patients with chronic previously reported respiratory diseases were excluded. Through this symptom diary it would be possible to quantify respiratory infections, their severity and duration. The questionnaire was subdivided in five main symptoms categories, similarly as occurred in the common cold questionnaire, but also including ear and eye symptoms. Furthermore allergy symptoms were included, namely nose and eye itching to exclude allergic symptoms in the evaluation of the symptoms diary. Patients were also requested to fill in if they had any symptoms and those symptoms reported in every and most of the days during the intervention study were excluded, as they were probably reported by patients with chronic respiratory diseases. The five domains were: general symptoms (shivering, muscle pain, tiredness, chest pain, dispnea), nasal symptoms (runny nose, obstructed nose, sneezing, nose itch), eye symptoms (itching eyes), throat symptoms (sore throat, itching throat, cough and hoarseness) and ear symptoms (ear pain) and body temperature. Temperature was

registered if the absolute value met above 37.5°C. Each symptom would be classified accordingly to the severity in a likert scale from 0 to 7.

A pilot study was performed with an elderly population already in an exercise program and due to difficulties in filling the Likert scale it was adapted to classification of the symptoms when present in mild, moderate or severe.

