All participants was given a symptom diary, and explained individually how it should be filled, also a written explanation was provided in the questionnaire itself. Symptoms diary should be filled daily if any of the symptoms was experienced. A contact to the investigator was provided if any questions or doubts were present. All participants were contacted telephonically each month to maintain compliance and questioned if they were still in the trial, if they had been sick or had any problem filling in the questionnaire. The questionnaire could also be filled by a third person if the participant was not able to read. In the nursing home the responsible for the elderly was also trained to know how the questionnaire should be filled.

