### Randomization and blinding

Patients will be informed of the procedure but they will be blinded to which is the intervention (high fat or low fat meal). Stratified blocked randomization will be performed accordingly to being asthmatic or obese. This methodology was chosen despite acute changes are the aim, to exclude and evaluate the intervention order in the studied outcomes. Equal number of participants will be allocated to each group.

Allocation concealment will be prevailed as investigator will only know the intervention order for that participant at the moment the meal is provided. Exercise challenge and outcome assessment, namely urine, blood sample collection, exhaled breath condensate and lung function will only be performed by another investigator blinded to the meal order.

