### **Respiratory infections symptoms diary (III)**

Symptom diary was built accordingly to the previously published respiratory infection assessment and after a pilot study to search for comprehensibility and adaptability to the population age [45, 46]. It was subdivided in five main symptoms categories: general symptoms (shivering, muscle pain, tiredness, chest pain, dyspnea), nasal symptoms (runny nose, obstructed nose, sneezing, nose itch), eye symptoms (itching eyes), throat symptoms (sore throat, itching throat, cough and hoarseness) and ear symptoms (ear pain) and body temperature. Temperature was registered, if the absolute value was above 37.5°C. Each symptom would be classified accordingly to the severity in mild, moderate or severe by the participant.

Respiratory infections were defined accordingly to symptoms assembly and period of time. Duration of respiratory infection was calculated accordingly to the symptoms that were correspondent to infection episode duration. Severity of the respiratory infections was classified as mild, moderate or severe, based in the type of symptoms and if they affected general health state of the individual.

Probable respiratory infection was defined by obtaining in at least three consecutive days, one of the four different settings:

- moderate or severe symptoms in two of five symptom categories (excluding the allergic symptoms namely nasal or ocular pruritus);
- mild/moderate symptoms in more than 3 symptom categories
- cough associated to at least 3 symptoms of 2 different symptom categories
- fever with other respiratory symptom.

Severity of respiratory infection was classified in: severe (participant had a systemic infection and/or severe local symptoms); moderate (mild systemic symptoms with moderate local symptoms) and mild (mild to moderate local symptoms).

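### Study III classifies infections from symptom diaries in an un-blinded trial, with some judgement left in the rules and nothing hiding the group from the reader

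*Protocol*

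**What the plan says.** Section 4.1.3 of the protocol describes Study III in these terms: "The study was a non-randomized, un-blinded, controlled trial targeting patients over 60 years". Infections come from a symptom diary kept during the 36-week programme, and the diary could be completed by someone else: "The questionnaire could also be filled by a third person if the participant was not able to read".

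The milestone table (section 7) places the laboratory work afterwards and adds that "statistical analysis will occur at the same time in order to evaluate which patients had respiratory infections".

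The definition of an infection is in section 4.2.1: "Probable respiratory infection was defined by obtaining in at least three consecutive days, one of the four different settings". Three of the four settings combine symptoms, symptom categories and grades. The fourth is "fever with other respiratory symptom". Before these are applied, section 4.1.3 removes background symptoms: "those symptoms reported in every and most of the days during the intervention study were excluded". Severity is graded separately, "based in the type of symptoms and if they affected general health state of the individual".

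No section says who classifies the diaries, whether that person knows the group, or that the rules are applied by a program. For Study IV, section 4.1.4 says that the exercise challenge and outcome assessment "will only be performed by another investigator blinded to the meal order".

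**The concern.** Training cannot be hidden from those who train. The diaries, however, are records that can be read without knowing who trained, and the protocol does not ask for that in Study III although it asks for a masked assessor in Study IV.

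This matters only where the reader has discretion. For infection yes or no there are two such places:

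- No threshold says how many days count as most of them. Removing a symptom as chronic can take a participant below the infection definition.
- The symptoms that qualify alongside fever are not listed.

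Duration depends on deciding which symptoms belong to an episode. Severity depends on effect on general health and on an undefined notion of systemic infection. Infection status is the outcome that section 4.3.2 analyses by relative risk and logistic regression. If the reader knows the group, these choices can lean one way, and adjusting for covariates later would not remove that.

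**Working it through.** **Where judgement enters**

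| Element | Place in protocol | Infection yes/no | Severity or duration |
|---|---|---|---|
| Three consecutive days, symptom-category rules | 4.2.1 | mechanical | – |
| Dropping symptoms present on most days | 4.1.3, diary | judgement (no threshold) | judgement |
| Fever plus an unlisted symptom | 4.2.1 | judgement (no list) | – |
| Which symptoms belong to the episode | 4.2.1 | – | judgement |
| Systemic infection, general health | 4.2.1 | – | judgement |

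**The plan's own figure.** Section 4.3.2 gives 30% power for 48% against 30% at alpha 0.05 with at most 40 per group. Full enumeration with Fisher's exact test, two-sided, 40 per group, gives 30.1%, so the figure reproduces. Masked reading changes none of these inputs.

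**Weight of one diary.** 38 participants were selected (section 4.1.3). Assume 19 per group. One diary moves a group's risk by 1/19 = 0.053, or 5.3 points.

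**Type I error under a lean in classification.** Assumptions not in the protocol: 19 per group and no true difference, with a common risk of 39%. That risk is the mean of the two planning risks, (48 + 30)/2, so it does not depend on which group carries which. The lean is an average of k diaries in one group re-read as not infected:

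- p1 = 0.39 − k/19, p2 = 0.39
- z = |a/19 − b/19| / √[p̄(1 − p̄)(2/19)], with p̄ = (a + b)/38
- rejection probability = Σ Bin(a; 19, p1) · Bin(b; 19, p2) over all a, b with z ≥ 1.96

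This z-test is the uncorrected Pearson chi-square named in section 4.3. Fisher's test, also named there, is shown beside it.

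| k | p1 | Pearson, 19 v 19 | Fisher, 19 v 19 | Pearson, 40 v 40 (p1 = 0.39 − k/40) |
|---|---|---|---|---|
| 0 | 0.390 | 5.8% | 2.8% | 5.1% |
| 1 | 0.337 | 7.2% | 3.5% | 5.7% |
| 2 | 0.285 | 11.5% | 6.2% | 7.4% |
| 3 | 0.232 | 19.2% | 11.4% | 10.6% |

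Repeating the 19 v 19 Pearson column with a common risk of 30% or 48% gives 11.4% and 10.9% for k = 2, and 21.0% and 18.2% for k = 3. The result depends little on the assumed risk.

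**A single null data set.** With 8 of 19 infected in each group, re-reading three diaries gives 5/19 against 8/19: ratio 5/8 = 0.625, Fisher p = 0.50. Re-reading two gives 6/19 against 8/19, p = 0.74. The estimate moves, but neither result becomes significant.

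**The case against.** The milestone sentence is a loose scheduling note that ties the statistics to the laboratory work. It is not an adjudication procedure. Timing is not the source of bias either; an unmasked reader is, whenever the reading is done. Both points stand. The concern therefore rests on the declared un-blinding and the absence of any masked reading, and the note shows only roughly when status is settled.

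The yes/no definition is mostly a matter of counting. This also stands. A reader might infer that the systemic and general-health wording makes infection status itself subjective, but in section 4.2.1 that wording belongs to severity.

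A reader might also infer that three re-read diaries could produce the whole protective effect for which the trial was planned. The documents do not support that comparison, because section 4.3.2 as written gives exercise 48% and control 30%, a ratio of 48/30 = 1.6. Nor do the documents show how many diaries are borderline.

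Removing names may not mask an investigator who made the monthly telephone calls or has already read the diaries. This stands and shapes the fix. Larger biases also remain: participants report their own symptoms knowing their group, and assignment followed availability and proximity. Masked reading does not touch these, but they are no reason to leave a separable bias in place.

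Programmed derivation and locking of outcome data are often left to an analysis plan, which is not at hand. Their absence alone would be no finding.

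**Conclusion.** The point holds in a limited form. Study III is un-blinded, its outcome is derived from diaries, nothing keeps the group from the reader, and two undefined steps leave some judgement in infection status, with more in duration and severity.

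The size is conditional. One diary is worth about 5 points of risk if the split is 19 and 19. An average lean of 2 to 3 diaries in one group takes the type I error from about 6% to about 12–19% with the uncorrected Pearson test, and to about 6–11% with Fisher's test, at an assumed common risk of 39%.

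It would go too far to say that a few diaries decide the result. In the single null example above, three diaries move the ratio to 0.625 and the p-value is still 0.50. The documents show that such bias is possible; they do not show that it occurred. The change is worth making because it is cheap and removes this one bias.

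**What to change.** - Enter the diaries under a code, with name, group, site and the identity of whoever filled them in removed.
- Before group is merged, fix the threshold for symptoms present on most days and the list of respiratory symptoms that qualify alongside fever.
- Apply the section 4.2.1 definition by program. Leave any remaining judgement, chiefly on duration and severity, to an existing team member who does not know the group and did not make the monthly calls.
- State in the protocol who classifies the diaries and that they do not know the group.

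The Study III analysis was due at Month 18 from September 2010, about February 2012, and the protocol is dated 10 December 2012. If classification has been done, repeat it in this way from the stored diaries, use that result, and report how the existing classification was made.

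The cost is data entry and programming for at most 38 diaries covering 36 weeks, with no added participants, visits or procedures and no effect on power. Masking may be imperfect for diaries completed by nursing-home staff, because controls were recruited in part from nursing homes.
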